#### Safety assessments

2.7.4

Safety evaluations include complete blood count, liver function (ALT, AST), and renal function (urea, creatinine). Assessment at baseline and Week 2.

### Safety monitoring and adverse event management

2.8

#### Recording and reporting of adverse events

2.8.1

All AEs and serious adverse events (SAEs) must be thoroughly documented in case report forms (CRF/eCRF), including event name, onset/offset dates, severity, interventions, clinical outcome, and investigator-assessed causality with study intervention. Investigators should provide prompt treatment upon identification of an AE and complete initial documentation. SAEs must be reported to the principal investigator and sponsor within 24 h and submitted to the ethics committee and regulatory authorities as required. Subjects who discontinue due to AEs should be followed until resolution, and outcomes recorded.

#### Management of intervention- and drug-related AEs

2.8.2

Common adverse reactions related to taVNS include local pruritus, burning sensation, erythema/bruising, transient dizziness, or device displacement. Upon occurrence, stimulation should be immediately discontinued and participant status assessed; parameters may be adjusted or treatment terminated if necessary. Device malfunctions should be reported following the device adverse event protocol.

For metformin-related gastrointestinal intolerance (e.g., diarrhea, nausea, bloating), management should be guided by severity, including symptomatic support, dose adjustment, or switching to extended-release formulations. Severe dehydration, electrolyte imbalance, or life-threatening complications require immediate drug discontinuation and SAE management. All interventions (outpatient care, medication adjustments, hospitalization, referrals) must be documented and followed until resolution.

#### Management of clinical deterioration

2.8.3

In the event that a participant experiences life-threatening conditions or requires hospitalization, all study-related procedures should be immediately suspended and emergency care initiated. The principal physician will assess the condition and determine whether continued participation is feasible.

For major safety events, the study principal investigator shall convene the DMC and Ethics Committee to conduct risk assessments and decide, based on independent recommendations, whether the trial should be paused or terminated.

### Safety evaluation

2.9

All AEs will be graded and analyzed according to standardized systems. For practical purposes, a simplified grading mapped to the CTCAE is applied as follows:

Grade 1 (Mild): Minor symptoms requiring no intervention or only simple supportive care.

Grade 2 (Moderate): Requires outpatient management or limitation of daily activities.

Grade 3 (Severe): Requires hospitalization or prolongation of hospitalization.

Grade 4 (Life-threatening): Requires emergency intervention or life support.

Grade 5: Death directly related to the AE.

Safety endpoints include incidence, severity distribution, onset timing, intervention-related causality of AE/SAE, and laboratory abnormalities (CBC, liver and renal function). Results are primarily descriptive, with between-group comparisons performed as appropriate. De-identified individual case information may be disclosed.

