#### Standard care (background therapy)

2.6.1

Background therapy follows international guideline recommendations and comprises standardized lifestyle counseling and medication management. Lifestyle counseling includes: dietary guidance with carbohydrates accounting for 45–60% of total daily energy intake and dietary fiber ≥25 g/day; at least 150 min/week of moderate-intensity aerobic activity (for example, brisk walking or cycling); and standardized education on disease management, medication adherence, and management of gastrointestinal symptoms to ensure consistency across participants (American Diabetes Association, 2024a,b).

Medication management principles are as follows:

Discontinue or avoid medications known to exacerbate gastrointestinal symptoms where clinically appropriate (e.g., stimulant laxatives or certain over-the-counter preparations);

In participants with inadequate glycaemic control, additional antihyperglycaemic agents (for example, SGLT2 inhibitors or DPP-4 inhibitors) may be added as clinically indicated, provided such additions are unlikely to aggravate gastrointestinal function; adjustments will follow current guideline recommendations and be documented;

Concomitant treatment for chronic conditions (e.g., antihypertensives for hypertension or secondary prevention therapies for coronary artery disease) will be maintained but clinicians should avoid introducing agents known to provoke GI intolerance when alternatives are available.

Metformin dosing will follow a “start low, escalate gradually” regimen: initial dose 500 mg administered with meals twice daily; dose titration will proceed weekly guided by fasting blood glucose (target 4.4–7.0 mmol/L), with a maximum dose up to 2,000 mg/day or the participant's maximal tolerated dose. Dose adjustments and all concomitant medications will be supervised and recorded by study physicians. In the event of severe, poorly tolerated diarrhea (e.g., ≥5 bowel motions per day with clinical signs of dehydration), metformin will be withheld or adjusted and symptomatic therapy provided (e.g., diosmectite); severe events will be managed according to the study Serious Adverse Event (SAE)—defined per the Common Terminology Criteria for Adverse Events (CTCAE) as any adverse event resulting in death, life-threatening illness, hospitalization, persistent disability, or requiring immediate emergency intervention—procedure and continue to be followed up (Rena et al., 2013).

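### Grade 3 (severe) is defined only by hospitalization, so no severe non-serious adverse event can be recorded, and diarrhoea the protocol calls severe grades as moderate unless the participant is admitted

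*Protocol article*

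**What the plan says.** Section 2.9 introduces the scale with "For practical purposes, a simplified grading mapped to the CTCAE is applied as follows". The grades that matter here are:

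- The severe grade, which has a single route in: "Grade 3 (Severe): Requires hospitalization or prolongation of hospitalization"
- One step below it, where events treated without admission fall: "Grade 2 (Moderate): Requires outpatient management or limitation of daily activities"
- One step above it: "Grade 4 (Life-threatening): Requires emergency intervention or life support"
- The top of the scale, for a fatal outcome: "Grade 5: Death directly related to the AE"

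The same section lists severity distribution as a safety endpoint, separate from incidence and from the causality of AEs and SAEs.

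Section 2.6.1 defines an SAE as "any adverse event resulting in death, life-threatening illness, hospitalization, persistent disability, or requiring immediate emergency intervention". It also gives an example of severe diarrhoea: "In the event of severe, poorly tolerated diarrhea (e.g., ≥5 bowel motions per day with clinical signs of dehydration". The response described is to withhold or adjust metformin and give symptomatic therapy. Admission is not mentioned. The sentence then sends severe events to the SAE procedure.

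Section 2.8.2 adds: "Severe dehydration, electrolyte imbalance, or life-threatening complications require immediate drug discontinuation and SAE management".

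**The concern.** Severity (how intense an event is) and seriousness (whether it meets regulatory outcome criteria) are different attributes, and an AE table needs both. Here the severe grade is defined by one of the seriousness criteria. An intense event handled in the outpatient clinic then has no grade above moderate.

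This matters in this trial because all participants are metformin-intolerant and receive metformin titrated upward as background therapy. Gastrointestinal events are both the condition under study and an expected harm. Outpatient gastrointestinal events that the protocol's own text calls severe would be pooled with ordinary moderate ones in the grade table. SAE status also sets the reporting duties in section 2.8.1, so an unclear label affects conduct as well as the final tables.

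**Working it through.** The documents give no figure to reproduce, and no arithmetic applies. The check sets the grades in section 2.9 against the SAE criteria in section 2.6.1, then runs the protocol's own diarrhoea example through the scale.

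**Step 1. From grade to SAE.**

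| Grade (2.9) | Route into the grade | SAE criterion met (2.6.1) |
|---|---|---|
| 1 | No intervention, or simple supportive care | None implied |
| 2 | Outpatient management or limited daily activities | None implied |
| 3 | Hospitalization or its prolongation | Hospitalization |
| 4 | Emergency intervention or life support | Life-threatening illness; emergency intervention |
| 5 | Death | Death |

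All three upper grades meet an SAE criterion. The SAE definition does not mention prolongation of a stay; I read hospitalization as covering it. On that reading the set of severe but non-serious events is empty by construction.

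**Step 2. From SAE to grade.** Four of the five SAE criteria (death, life-threatening illness, hospitalization, emergency intervention) fall in Grades 3 to 5. The fifth, persistent disability, has no matching grade and can sit below Grade 3 if the participant is not admitted. The overlap is near-complete but not exact.

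**Step 3. The diarrhoea example.** Take a participant with five or more motions a day and signs of dehydration, managed as section 2.6.1 describes.

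- Not admitted, and no emergency intervention needed: the event fits Grade 2 (moderate). It cannot be Grade 3. Section 2.6.1 calls it severe.
- Admitted: the event is Grade 3 and an SAE. The sections agree.

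The mismatch therefore depends on non-admission.

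**Step 4. SAE status of the non-admitted case.** Two readings are open.

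- If severe events go to SAE handling because they are severe, the event is handled as an SAE, is graded 2, and need not meet the SAE definition in the same sentence.
- If only events that meet the definition go there, the event is not an SAE. It is then called severe in section 2.6.1, graded moderate in section 2.9, and classed as non-serious.

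The second reading removes the routing conflict but leaves the conflict between severe and moderate. Section 2.8.2 raises the same question for severe dehydration, which goes to SAE management with no condition on admission.

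**The case against.** The strongest reply is that severe in section 2.6.1 is a management trigger given by example, not a grade. Because the SAE definition sits in the same clause, a natural reading is that only events meeting it go to the SAE procedure. The scale is openly a simplification, this is a 60-participant pilot, safety results are mainly descriptive, and section 2.8.1 already requires severity, interventions, outcome and causality to be documented for each event.

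That lowers the stakes and makes the routing conflict a matter of interpretation. It does not give Grade 3 a route other than hospitalization. Section 2.9 says the scale is applied to all AEs, so this is a stated rule and not detail left to a fuller document.

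Two stronger readings are tempting, and the documents support neither.

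- A reader might infer that the severity endpoint merely copies the SAE count. It does not. The endpoint includes the Grade 1 versus 2 split, which carries information of its own. Even at Grade 3 and above the match is inexact, because persistent disability has no grade and any non-admitted event handled as an SAE would be Grade 2.
- A reader might infer that an arm difference in severe outpatient gastrointestinal events would be hidden. It would be blurred in the AE grade table only. The Metformin Symptom Severity Score rates nausea, bloating or pain, and diarrhoea by frequency and by 1-to-5 severity. Stool form and urgency are recorded daily, and medication adjustments and outpatient care must be documented.

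**Conclusion.** The point holds as a defect in a stated rule. Section 2.9 makes hospitalization the only way into Grade 3, so Grades 3 to 5 all lie within the SAE definition and a severe non-serious event cannot be recorded. Diarrhoea of the kind section 2.6.1 calls severe is Grade 2 when managed without admission, and sections 2.6.1 and 2.8.2 leave its SAE status unclear.

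The consequence is a loss of information at the upper end of the severity distribution, and possible inconsistent labelling of the same event. The number of events affected cannot be estimated: the Introduction cites rates of any diarrhoea on metformin from another trial, but the document gives no expected rate of severe events or of admissions.

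The conclusion assumes that prolonged hospitalization counts as hospitalization in the SAE definition. It does not depend on what CTCAE itself says, which the document does not reproduce and which was not judged here. It should be corrected, but it does not threaten the pilot's main aims.

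**What to change.** Reconcile sections 2.6.1, 2.8.2 and 2.9 so that severe has one meaning and it is clear which events enter SAE handling.

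- Grade severity by symptom intensity and functional impact, independently of care setting, or use the event-specific CTCAE grades to which section 2.9 says its scale maps.
- Record seriousness as a separate yes/no field with its own criteria.
- Report severity and seriousness separately by arm.

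The cost is protocol wording and one case report form field, with no extra visits or tests. No change to dosing, withholding of metformin or any other clinical management is proposed.

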### Statistical methods

2.10

All data will be managed according to GCP guidelines for clinical trials. Two independent researchers will perform double data entry for all variables, including bowel urgency scores, glucose and insulin metabolism markers, serum inflammatory markers, and safety parameters. Cross-verification is mandatory, and the database will be locked without authorization.

Statistical analyses will be performed by blinded biostatisticians using SAS 9.4 and R 4.2.1. Two analysis sets will be applied: the intention-to-treat (ITT) set includes all randomized participants, and the per-protocol (PP) set includes participants completing ≥80% of the treatment course without major protocol violations, for sensitivity analysis.

Baseline characteristics will be summarized by group. Continuous variables are assessed for normality using the Shapiro–Wilk test: normally distributed variables are presented as mean ± SD, non-normal as median [IQR]; variance homogeneity is assessed via Levene's test. Categorical variables are expressed as counts (*n*) and percentages (%). Between-group comparisons: independent *t*-test or Mann–Whitney *U*-test for continuous variables, Pearson χ^2^ or Fisher's exact test for categorical variables.

Primary and continuous outcome variables (bowel urgency score, FBG, PG2h, FINS, C-peptide, HOMA-IR, ISI, GA, serum IL-6/IL-10/TNF-α, GLP-1, 5-HT, D-lactate, diamine oxidase, and fecal bile acids) will be analyzed using linear mixed-effects models (fixed effects: group, time, interaction; random effect: participant), reporting least-squares means with 95% *CI*. The exact mathematical formulas and covariance structures for these linear mixed-effects models will be fully reported in the final trial publication. Categorical outcomes are analyzed via χ^2^ or Fisher's exact test.

A Multiple Imputation (MI) model will be used as the primary method for missing data. The imputation model will include all primary and secondary outcomes, plus baseline covariates (age, sex, duration of diabetes, baseline metformin dose, baseline Metformin Symptom Severity Score score), with 20 Markov Chain Monte Carlo iterations to generate 20 imputed datasets. The pre-specified linear mixed-effects model will be performed on each dataset, with results pooled via Rubin's rules (Heymans and Twisk, 2022).

Complete case analysis will be conducted as a sensitivity analysis to verify the robustness of the core findings. Exploratory subgroup analyses stratified by age, sex, and diabetes duration are descriptive only.

The success of blinding will be evaluated using the James BI for all participants and independent outcome assessors at Week 2 and Week 4. The BI is scaled from 0 (all participants guessed correctly) to 1 (all participants guessed incorrectly), with 0.5 indicating completely random guesses (the standard for successful blinding). Weights are assigned consistent with the original James method: 0.00 for correct guesses, 1.00 for incorrect guesses, and 0.50 for uncertain/unable to judge responses, with uncertain responses split equally between correct and incorrect guesses. The BI and its 95% CI will be calculated using the jack-knife procedure recommended in the original method (James et al., 1996).

Safety parameters (CBC, ALT, AST, urea, creatinine) are analyzed similarly, comparing abnormality rates. All tests are two-sided with α = 0.05; effect sizes are reported with 95% CI.

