### Randomization and blinding

2.5

Participants will be randomized 1:1 to taVNS group or sham control group, with stratification by age and gender to balance baseline characteristics between groups. The randomization sequence will be generated by an independent third-party biostatistician using SPSS 26.0, with group allocation sealed in sequentially numbered, opaque envelopes for strict allocation concealment. After baseline assessment, a dedicated study coordinator (fully blinded to group assignment) will open envelopes in numerical order to assign eligible participants.

Given the anatomical specificity of active and sham stimulation sites, intervention staff responsible for electrode placement and device operation cannot be blinded to group allocation. To mitigate potential bias, we have implemented pre-specified rigorous safeguards: The blinded coordinator exclusively manages group allocation, and only provides intervention staff with pre-marked anatomical diagrams of stimulation sites, with no disclosure of group identity at any time. Non-blinded intervention staff are strictly barred from outcome assessment, data entry, statistical analysis, or any communication with participants about group allocation or expected intervention effects. Both groups use identical stimulators with consistent nominal parameters; all intervention staff receive centralized standardized training to ensure identical operational execution and participant interaction across groups.

All outcome assessors, data analysts, biostatisticians, and participants will remain fully blinded to group allocation throughout the trial. Furthermore, treating physicians are solely responsible for routine clinical management and safety assessments; they have no access to group allocation and are strictly isolated from intervention implementation and outcome assessment. Participants will be informed that both interventions may induce a mild tingling sensation, and subjective feeling cannot be used to infer group assignment, to minimize anticipation bias. Outcome assessors will receive standardized training and regular inter-rater reliability checks to reduce measurement bias.

The effectiveness of the blinding will be formally assessed in Weeks 2 and 4 using the validated James Blinding Index (BI) method (James et al., 1996). The detailed statistical procedures for this assessment are outlined in the “Statistical Methods” section.

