#### Primary efficacy outcome and assessment time points

2.7.2

The primary efficacy endpoint is the total score of the Metformin Symptom Severity Score, a validated, widely used self-report tool originally developed and psychometrically validated by McCreight et al. specifically for evaluating metformin-related gastrointestinal intolerance in adults with T2DM (McCreight et al., 2018).

In the original validation study by McCreight et al., this questionnaire demonstrated excellent reliability and validity: it showed strong internal consistency (Cronbach's α > 0.8), good test-retest reliability, and significant discriminant validity, with a highly significant difference in total scores between metformin-intolerant and metformin-tolerant patients (*P* < 0.0001) (McCreight et al., 2018). The questionnaire covers medication adherence, reasons for discontinuation, dose tolerance, gastrointestinal symptoms (nausea, abdominal bloating/pain, and diarrhea; frequency and subjective severity), changes in baseline symptoms, and an overall subjective tolerance rating, with a total score ranging from 0 to 50 points (0–10 = tolerable, 11–20 = mild intolerance, 21–30 = intolerable, 31–50 = severe intolerance). This questionnaire is used for the quantitative assessment of intolerance-related symptoms in this trial, not as a basis for clinical diagnosis.

Assessment time points include baseline, Week 2, and Week 4. Details of the questionnaire items and scoring criteria are provided in Table 2 (McCreight et al., 2018).

**Table 2 T2:** The metformin symptom severity score questionnaire.

No	Question	Option	Score
1	Are you still taking metformin?	Yes (skip to question 6)	0
		No	5
2	If you have stopped taking metformin, was it due to side effects?	Yes (continue to question 3)	5
		No (skip to question 6)	0
3	What dose were you taking at the time of discontinuing metformin?	500 mg once daily (1 tablet)	4
		1,000 mg once daily (2 tablets)	3
		500 mg twice daily (2 tablets)	2
		2,000 mg once daily (4 tablets)	1
		1,000 mg twice daily (2 tablets)	0
4	Have you ever taken a lower dose of metformin and tolerated it well?	Yes	0
		No	1
	If yes, what was the maximum dose you tolerated?	(e.g., 500 mg once daily)	2
5	Have you been trialed on a modified release preparation of metformin (e.g. Glucophage SR)?	Yes	2
		No	0
In the last week of taking metformin, have you experienced?			
6	Nausea?	Yes	1
		No	0
	If yes, how often?	More than once a day	4
		Once a day	3
		Occasionally	2

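### The mixed model for the primary score omits the baseline score and the age and sex stratification factors, so the effect-size estimate is less precise than the collected data allow

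*Protocol article*

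**What the plan says.** All places are in the protocol article.

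- **Model (2.10 Statistical methods).** The terms are listed as "fixed effects: group, time, interaction; random effect: participant", with least-squares means and 95% confidence intervals as the output. The section also states: "The exact mathematical formulas and covariance structures for these linear mixed-effects models will be fully reported in the final trial publication".
- **Randomization (2.5).** Allocation is 1:1, "with stratification by age and gender to balance baseline characteristics between groups". The age cut-points are not given.
- **Primary endpoint (2.7.2).** "The primary efficacy endpoint is the total score of the Metformin Symptom Severity Score". On timing: "Assessment time points include baseline, Week 2, and Week 4". No visit is singled out.
- **Imputation (2.10).** The imputation model contains the outcomes "plus baseline covariates (age, sex, duration of diabetes, baseline metformin dose, baseline Metformin Symptom Severity Score score").
- **Baseline data (2.7.1).** Baseline characteristics are said to serve for confounder control, but no term in the listed model does this.
- **Purpose (2.4 and the Abstract's Discussion).** The trial is sized to estimate the outcome's standard deviation and plans no formal efficacy test. Effect-size estimates for later confirmatory trials are a stated product.

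**The concern.** In a randomized trial with a continuous score measured before and after treatment, the baseline score is usually the strongest available predictor of the follow-up score. A model with only group, time and their interaction either subtracts baseline in full (difference in change) or does not use it (difference in visit means). Adjustment lets the data choose the weight.

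The stratification factors raise a related question. If they predict outcome, leaving them out of a between-participant comparison puts variance that the design has already balanced back into the standard error.

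With about 25 evaluable participants per arm the interval will be wide in any case. That interval is what the designers of a confirmatory trial will read, and the covariates that would narrow it are already in the database.

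**Working it through.** **1. The plan's own figures.** 30 × 0.85 = 25.5, taken as 25 per arm. 25 + 25 − 2 = 48 degrees of freedom. 25 / 0.85 = 29.4, so 30 per arm and 60 in total. These reproduce section 2.4.

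**2. Which effect does the model give?** Baseline is probably a level of time. The same model is applied to the cytokines and gut markers, which sections 2.7.3.4 and 2.7.3.5 place at baseline and Week 2 only. Without baseline as a level, these would have one visit and no time term. (Table 1 marks these markers at Week 2 only, so this inference rests on the text sections.) On this reading the group-by-time term is a difference in change. The alternative is a difference in least-squares means at a visit. The article does not say which is meant.

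**3. Variances.** Let r be the correlation between baseline and follow-up score, with equal variance σ² at each visit and n per arm. In units of 2σ²/n:

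- visit difference: 1
- difference in change: 2(1 − r)
- baseline-adjusted difference: 1 − r²

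The adjusted variance relative to change is (1 − r²) / [2(1 − r)] = (1 + r)/2. Relative to the visit difference it is 1 − r².

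The documents do not give r, so the values below are assumptions. Half-widths of the 95% interval are in SD units for n = 25 per arm: t × √(2/25 × variance), with 48 degrees of freedom unadjusted and 47 adjusted.

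| Assumed r | Adjusted ÷ change | Adjusted ÷ visit | Half-width, change | Half-width, visit | Half-width, adjusted |
|---|---|---|---|---|---|
| 0.3 | 0.65 | 0.91 | 0.673 | 0.569 | 0.543 |
| 0.5 | 0.75 | 0.75 | 0.569 | 0.569 | 0.493 |
| 0.7 | 0.85 | 0.51 | 0.441 | 0.569 | 0.406 |

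Relative to the adjusted interval, the change interval is about 24%, 15% and 8% wider, and the visit interval about 5%, 15% and 40% wider. At r = 0.5 either reading needs 1/0.75 = 1.33 times the sample for the same precision. For the change reading at r = 0.7 the factor is 1/0.85 = 1.18.

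The ordering does not depend on equal variances. With SDs σ₀ and σ₁ at baseline and follow-up, the change variance minus the adjusted variance is σ₀² + σ₁² − 2rσ₀σ₁ − σ₁²(1 − r²) = (σ₀ − rσ₁)², which is never negative.

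**4. Age and sex, change reading.** If age and sex shift a participant's score by the same amount at every visit, the shift drops out of follow-up minus baseline. In a simulated complete data set (25 per arm, three visits, random intercept, prognostic age and sex), the standard error of the interaction was 0.26695 both with and without the two covariates.

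**5. Age and sex, visit reading.** In a simulation with four balanced age-by-sex strata, 24 per arm and 20,000 runs, the share R² of outcome variance explained by age and sex was assumed, because the documents do not give it.

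| Assumed R² | Coverage of nominal 95% interval, factors omitted | Narrowing when included |
|---|---|---|
| 0 | 95.2% | about 0% |
| 0.05 | 95.5% | about 3% |
| 0.1 | 96.5% | about 5% |
| 0.2 | 97.3% | about 11% |
| 0.3 | 98.0% | about 17% |

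The error is conservative, and it disappears if age and sex are not prognostic.

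**The case against.** A group-by-time mixed model with baseline among the responses is a standard and valid analysis under randomization. Covariate adjustment improves efficiency and does not remove a bias. The trial is a pilot sized on the standard deviation, and its 48 degrees of freedom for that purpose do not depend on this choice. All of this stands. It limits the size of the point without removing it, because effect-size estimates are also a stated product and the listed model is less precise for them.

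A reader might infer three stronger things that the article does not support.

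- **That the planned interval is wrong because it ignores the stratification.** On the likelier reading, age and sex effects that are constant over time cancel. On the other reading, the interval errs on the wide side.
- **That the covariance structure will be chosen after the data are seen.** The sentence on formulas and covariance says where they will be reported, not when they are decided. The same section calls the model pre-specified and has blinded statisticians run it.
- **That Week 2 and Week 4 are both primary time points.** Section 2.7.2 lists assessment times, baseline included, and ranks none. The unnamed visit and the covariance structure are details that a statistical analysis plan may supply, and would not be a finding on their own.

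**Conclusion.** The point holds as one of precision. The article closes the list of model terms without the baseline score, and on either reading of the treatment effect the result is less precise than a baseline-adjusted difference. This is true against the visit difference for any r between 0 and 1, and against the difference in change for any r below 1 when the variances are equal.

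For assumed r of 0.3 to 0.7, adjustment reduces the variance by 15% to 35% against the difference in change, and by 9% to 49% against a visit difference. The formulas leave aside the small cost of estimating the baseline slope.

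The stratification part is conditional. It matters only for a visit-level group difference and only if age and sex predict the score. Complete data and effects that are constant over time leave the group-by-time contrast untouched.

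It would be tempting to call this a loss of power. The documents do not support that, since no efficacy test is planned. What is lost is precision in the effect-size estimate and its interval. The planned analysis is not invalid.

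**What to change.** In section 2.10, or in the analysis plan before unblinding:

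1. Fit the mixed model to the Week 2 and Week 4 scores, with fixed effects for baseline score, baseline score by visit, age and sex as used in the randomization, group, visit and group by visit. An equivalent route is to keep baseline among the responses and constrain the two groups' baseline means to be equal.
2. Name one visit's adjusted between-group difference, with its 95% confidence interval, as the main estimate. Week 2, the end of treatment, is one candidate; the choice is the sponsor's.
3. Apply the same baseline adjustment to every continuous secondary outcome that has a baseline measurement.

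The cost is analysis wording and a few degrees of freedom. The covariates are already collected and already enter the imputation model.
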